## Abstract

**Introduction:**

Osteoporotic hip fractures present a significant global challenge to patients, clinicians and healthcare systems. It is estimated that hip fracture accounts for 1.4% of total social and healthcare costs in the established market economies.

**Methods and analysis:**

The World Hip Trauma Evaluation (WHiTE) was set up to measure outcome in a comprehensive cohort of UK patients with hip fracture. All patients in the cohort are treated under a single comprehensive treatment pathway. A core outcome set, including health-related quality of life, is collected on all the patients. This protocol describes the current multicentre project that will be used as a vehicle to deliver a series of embedded observational studies.

**Ethics and dissemination:**

Research Ethics Committee approval was granted (Rec reference 11/LO/0927, approved 18/8/2011) and each hospital trust provided National Health Service (NHS) approvals.

**Trial registration number:**

The study is registered with National Institute of Health Research Portfolio (UKCRN ID 12351) and the ISRCTN registry (ISRCTN63982700).

## Introduction

The World Hip Trauma Evaluation (WHiTE) project was set up to measure outcome in a comprehensive cohort of UK patients with hip fracture. All patients in the cohort are treated under a single comprehensive treatment pathway. A core outcome set, including health-related quality of life (QoL), is collected on all the patients.

This protocol describes the current multicentre project that will be used as a vehicle to deliver a series of embedded observational studies.

Osteoporotic hip fractures present a significant global challenge to patients, clinicians and healthcare systems. It is estimated that hip fracture accounts for 1.4% of total social and healthcare costs in the established market economies.^1^ Approximately 8.5% of patients with hip fracture will die within 30 days of injury^2^ and 22.5% within 12 months.^2^
^3^ In addition, the majority of survivors experience a significant reduction in health-related QoL.^4^
^5^ The challenge is expected to intensify with a rise from the 1.3 million hip fractures in 1990 to 6.3 million globally by 2050.^6^

The National Hip Fracture Database (NHFD) already captures data on almost all patients with hip fracture in England, Wales and Northern Ireland.^7^ Although it is used principally for national clinical audit, there is considerable potential to use the NHFD for research purposes.^3^ However, the NHFD does not routinely capture patient-reported outcome measures and there is substantial variation in clinical decision-making (eg, choice of fixation device) between hospitals and individual surgeons, which risks introducing confounding to observational studies embedded within the NHFD.^8^

In order to address these limitations, we established the Warwick Hip Trauma Evaluation (WHiTE) study to measure outcome in a comprehensive cohort of hip fracture patients within the framework of the NHFD.^9–13^ This study was renamed ‘World Hip Trauma Evaluation’ following the decision to make the project multicentre in 2015. The WHiTE project is nested within the NHFD and all patients are treated under a single comprehensive treatment pathway that is based on the National Institute for Health and Care Excellence (NICE) Hip Fracture Guidelines.^14^ This should help limit unexplained variability in clinical decision-making. The WHiTE project will also enrich the NHFD data by collecting patient-reported outcome measures and functional status after discharge from hospital. These are included within a ‘core outcome set’ that has been established for this patient group; both outcome measures and data collection systems were tested in a series of single-centre pilot investigations.^11–13^

As WHiTE is nested within a clinical registry, it will capture variables (eg, fracture pattern and operation type) that are particularly important for hip fracture research. The data are also collected prospectively by dedicated research associates at each hospital site for the principle purpose of research. It will therefore provide a richer resource for hip fracture research than existing UK administrative data sets, such as Hospital Episode Statistics (HES) and the Clinical Practice Research Datalink (CPRD).

### Objective

The objective of the WHiTE project is to provide a data collection framework in which a series of observational studies can be embedded by hip fracture researchers.

## Patients and methods

### Eligibility

All patients presenting with a hip fracture to one of the recruiting National Health Service (NHS) sites and who would currently be reported to the NHFD. Alignment with the NHFD eligibility criteria will reduce the data collection burden at recruiting sites, which is important for its sustainability as further studies are embedded within the WHiTE framework. The NHFD exclusion criteria are:
Age <60 years.Non-operative treatment.^7^

Throughout the study, screening logs will be kept to determine the number of patients assessed for eligibility and reasons for any exclusion. Patients who decline to consent to take part will be given the opportunity to inform the research team of the reasoning behind their decision not to participate.

### Consent

Patients with a hip fracture are a clinical priority for urgent operative care and will usually undergo surgery on the next available trauma operating list. All WHiTE recruiting sites treat hip fracture patients according to national guidelines and so patients will be managed according to a series of common standard treatment pathways. The WHiTE study will not affect their treatment in any way. The patients will be approached for consent to be part of this cohort study in the immediate postoperative period.

At the first appropriate time when the patient has regained capacity (usually the first day after surgery) a research associate will provide the participant with the study information. The patient will be given the opportunity to ask questions and discuss the study with their family and carers for as long as they require. They will then be asked to provide written consent to participate in the study. If the patient does not wish to complete questionnaires for the study at this stage, they will be asked if they are happy to provide written consent for us to access and use any routine NHS data, including that collected through the NHFD. Alternatively the patient can choose to decline to have any data entered into the study.

Best efforts will be made to involve participants who, temporarily or permanently, lack capacity in the decision to be involved in the study. The clinical team will make a judgement about the amount and complexity of the information that the participant is able to understand and retain on an individual basis. Appropriate information will be communicated to the participant and updated as their understanding changes. In the event that a patient has temporary loss of capacity, we will follow best practice and ask the patient for consent as soon as they are able to do so.

In accordance with section 32 subsection 9b of the Mental Capacity Act 2005, where a patient does not have capacity to consent for themselves, we will seek agreement from an appropriate consultee.

Where a personal consultee is available, they will be provided with the study information. The personal consultee will be given the opportunity to ask questions and discuss the study after which they will be asked to provide agreement, which will be documented. The personal consultee will complete the outcome questionnaires on behalf of the patient.

Where a personal consultee is not available, a nominated consultee will be identified to advise the research team. This person will be the patient's treating surgeon and/or their treating general practitioner. If their surgeon is a member of the research team, another independent surgeon will be identified.

If the patient withdraws from the study, data collected up until the point of withdrawal will be included in any subsequent analyses.

At all times the chief investigator will act in accordance with the patients' best interests. Any new information that arises during the trial that may affect participants' willingness to take part will be reviewed by the Oversight Committee; if necessary this will be communicated to all participants and a revised consent form completed.

### Standardised treatment pathway

Participants will be treated in accordance with a standardised care pathway from diagnosis to final discharge from hospital. This pathway is described below and is in accordance with national guidance issued by NICE.^14^

*Preoperative assessments*: Participants will usually be assessed in the emergency department. Diagnosis of a fracture of the hip will be confirmed by appropriate radiographic images. Where there is doubt over the presence or the radiological pattern of the fracture, further imaging will be performed as per routine clinical practice.

All participants will have initial assessment as part of a multidisciplinary pathway and will undergo the following investigations as a minimum: ECG, full blood count, group and save, and tests of renal function. A cognitive assessment will be undertaken.

Routine thromboprophylaxis will be started in all participants not already receiving anticoagulant therapy. Chemical and mechanical prophylaxis measures will be used in accordance with current protocols agreed at each centre.

*Anaesthetic technique*: A regional or general anaesthesia technique will be used for every participant. The anaesthetic procedure may incorporate a local anaesthetic nerve block using either a nerve stimulator or ultrasound-guided technique or periarticular analgesic injections in accordance with local protocols.

*Fracture pattern*: Fracture patterns will be classified preoperatively from the radiographs into four groups:
Group 1: undisplaced/valgus impacted intracapsular;Group 2: displaced intracapsular;Group 3: trochanteric—fractures centred within the trochanteric region;Group 4: subtrochanteric—fractures centred within the region 5 cm below the lesser trochanter.

*Operative intervention*: All participants should aim to have surgery on the day or the day after injury on a consultant-led operating list. All participants will receive perioperative prophylactic antibiotics in accordance with current protocols agreed at each centre.
*Group 1: undisplaced intracapsular fractures*: all participants will have their fracture fixed in situ. Internal fixation of the fracture will be achieved through a standard mini open lateral or percutaneous approach with parallel cannulated screws.*Group 2: displaced intracapsular fractures*: the operating surgeon will perform their preferred approach. The hip will be dislocated and the head excised. There are two subgroups:
The majority of patients with low prefracture functional demand—a proven hemiarthroplasty femoral component will be cemented into the femur using a third generation cementing technique.A subgroup of patients with high prefracture functional demand—total hip replacement (THR), where the acetabulum is also replaced. Given the lack of evidence to support criteria to select those participants who might benefit from THR a pragmatic approach will be adopted. Eligibility for this subgroup will be determined by the treating orthopaedic surgeon, on the basis that he or she believes the participant would benefit from total hip arthroplasty. In the event of a participant undergoing THR the approach, implant and operative technique employed would be at the discretion of the operating surgeon.*Group 3: trochanteric fractures*: All participants will undergo reduction of their fracture on a fracture table. There are three subgroups:
Stable standard-obliquity fractures (AO/OTA A1)—internal fixation with a sliding hip screw.Unstable standard-obliquity fractures (AO/OTA A2)—internal fixation using a sliding hip screw.Unstable reverse obliquity or fractures at the level of the lesser trochanter (AO/OTA A3)—internal fixation with a distally locked, cephalomedullary device.*Group 4: subtrochanteric fractures*: All participants will undergo reduction of their fracture on a fracture table. Internal fixation of the fracture will be achieved using a distally locked, cephalomedullary device.

*Postoperative rehabilitation*: Post-operative analgesia will be prescribed perioperatively and reviewed by the responsible clinical teams as appropriate. In the postoperative period, participants will undergo an initial physiotherapy and occupational therapy trauma assessment. A full social, cognitive, premorbid function and falls history will be obtained and documented. An initial rehabilitation plan will be followed with all participants. All patients will undergo both a bone health assessment and falls risk assessment as per usual care.

*Discharge from hospital*: Participants will be discharged from the acute orthopaedic trauma ward at the earliest safe opportunity to the most appropriate discharge destination as determined by the multidisciplinary team.

### Outcome data

In this study, we will use techniques common in long-term cohort studies to ensure minimum loss to follow-up.

We will attempt to contact the patient or next of kin by telephone. If this fails we will send the patient or next of kin a postal questionnaire to complete with a prepaid return envelope. Finally the general practitioners of those participants who are deemed ‘lost to follow-up’ will be contacted in order to attempt to complete the follow-up. If all these methods fail, then we will class the patient as a non-responder for that time point.

*Health-related QoL score (EQ-5D)*: EuroQol (EQ-5D-5L) at 4 months postinjury, adjusted for preinjury score. The EQ-5D-5L is a validated self-administered patient-reported outcome measure and requires 5 min to complete. EQ-5D is a generic health-related QoL measure consisting of five dimensions each with a five-level answer possibility. Each combination of answers produces a health profile which can be converted into an estimated health utility score after applying a set of preference weights.^15^ The preliminary English social value set obtained from general population preferences will be used^16^ to estimate health utilities until one for the UK is produced and made available. The EQ-5D has good test–retest reliability, is simple for patients to use, and gives a single preference-based index value for health status that can be used for broader cost-effectiveness comparative purposes.

*Residential status*: Prefracture and current residential status will be collected at 4 months. The possible responses for residential status are: own home/sheltered housing, residential care, nursing home, rehabilitation unit, acute hospital, dead, other.

*Mobility status*: Prefracture and current mobility status will be collected at 4 months. The possible responses for mobility status are: freely mobile without aids, mobile outdoors with one aid, mobile outdoors with two aids or frame, some indoor mobility but never goes outside without help, no functional mobility (using lower limbs).

*Hospital information*: *Admission* including admission dates and orthopaedic/orthogeriatrician details. *Assessment* including Abbreviated Mental Test Score, pathological fracture and preoperative medical assessment information along with fracture classification and side. *Treatment* including operation details. *Discharge* including discharge summary.

*Complications*: The complications that we will report as ‘expected’ following hip fracture are: wound infection, respiratory infection, urinary tract infection, venous thromboembolism, cerebrovascular accident, cardiac event, failure of fixation, dislocation, blood transfusion.

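### As worded, prefracture residence and mobility are collected at the 4-month contact, so these baseline values may be recalled after the outcome and are at risk of being missing in patients who die first

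*Protocol article*

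**What the plan says.** Under Outcome data, the article gives the same timing for two status measures: "Prefracture and current residential status will be collected at 4 months" and "Prefracture and current mobility status will be collected at 4 months". The same section describes how follow-up is obtained. It begins "We will attempt to contact the patient or next of kin by telephone", goes on to a postal questionnaire and then the general practitioner, and if all of these fail, "then we will class the patient as a non-responder for that time point". Under End of study, contact may be made up to 3 months after the 4-month point.

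The section's Hospital information paragraph lists study items from the admission. Its assessment items are described as "including Abbreviated Mental Test Score, pathological fracture and preoperative medical assessment information along with fracture classification and side". Prefracture residence and mobility are not named there.

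Under Standardised treatment pathway, the postoperative rehabilitation paragraph says: "A full social, cognitive, premorbid function and falls history will be obtained and documented". This is described as part of care. The article does not say that it is the source of the study's prefracture variables.

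**The concern.** Prefracture residence and mobility are baseline characteristics. They are the reference for any loss of independence and obvious candidates for adjustment. The Introduction names confounding as the weakness of registry studies that the project is meant to limit, and the pathway makes prefracture functional demand the basis for choosing between two operations for displaced intracapsular fractures. A comparison of those operations would want a prefracture mobility value that does not depend on how the patient fared.

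Taken as written, the timing rule causes two problems:

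- **Recall.** The respondent reports prefracture status knowing the recovery. Error in the baseline value can then be related to the outcome. This affects change from prefracture status, where baseline and outcome come from the same contact, and any model that adjusts for the recalled value.
- **Availability.** For a patient who dies before the contact, the value must come from a proxy or the general practitioner. For a non-responder it is not obtained. Patients who decline questionnaires and allow only routine data, as the Consent section permits, would not be expected to supply it by this route at all.

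The second problem bears most on mortality analyses. The Sample size section names the death rate as a question already known to be important.

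**Working it through.** The article states no figure on this point, so there is none to reproduce. The check has two parts.

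**Where the values could come from**

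| Section | Content | Makes the admission the study source? |
|---|---|---|
| Outcome data, residence and mobility | Prefracture and current status at 4 months | No, it states 4 months |
| Outcome data, Hospital information | Admission, assessment, treatment, discharge | The two items are not named |
| Standardised treatment pathway | Social and premorbid history documented in hospital | Information exists, but as care |
| Introduction | The project will "enrich the NHFD data by collecting patient-reported outcome measures and functional status after discharge from hospital" | Concerns status after discharge |
| Outcome data, EQ-5D | "EuroQol (EQ-5D-5L) at 4 months postinjury, adjusted for preinjury score" | Collection time of the preinjury score not given |

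The only collection time stated for these two items is 4 months. With the 3-month allowance, the report comes 4 to 7 months after surgery.

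**How many patients are exposed**

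Inputs from the article: mortality 8.5% at 30 days and 22.5% at 12 months (Introduction); target 6000, example subgroup 325, and 90% follow-up at 4 months (Sample size). Four-month mortality is not given and is an assumption here, with 30 days taken as month 1.

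1. Linear interpolation: 8.5 + (22.5 − 8.5) × 3/11 = 12.3%.
2. Constant hazard from month 1 to month 12: 1 − 0.915 × (0.775/0.915)^(3/11) = 12.6%.
3. Deaths before contact: 6000 × 0.1232 = 739 and 6000 × 0.1255 = 753, so about 740 to 755. In the 325-patient subgroup, about 40 to 41.
4. Outer bounds, using the two stated rates themselves: 6000 × 0.085 = 510 and 6000 × 0.225 = 1350. In the subgroup, about 28 to 73.

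For overall loss, let the 10% non-response apply to survivors:

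5. Non-responders: (6000 − 739) × 0.10 = 526.
6. No value obtained for any deceased patient: 739 + 526 = 1265, and 1265/6000 = 21.1%.
7. Proxies or records supply every deceased patient: 526/6000 = 8.8%. If the 10% instead applies to all 6000 with the dead counted as followed up, the loss is 600/6000 = 10%. Hence about 9-10%.

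The size of any recall error cannot be computed from the article.

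**The case against.** The best reply is that the two sentences are compressed and mean prefracture status, plus current status at 4 months. One response list that includes death serves both, which cannot be literal for prefracture residence. Other parts of the article point to collection in hospital: research associates collect data prospectively at each site, questionnaires appear to be offered at consent, baseline demographic data are mentioned, and the hospital items are introduced as examples. This is a fair reading of intent. But none of those places assigns prefracture residence or mobility to baseline, and under this reading the timing sentences are still worded wrongly and need the same correction.

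Three stronger inferences are tempting, and the objection defeats each of them:

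- **That the values are certainly missing for the dead.** Next of kin and general practitioners can be contacted, death is a recordable residential status, and an inpatient history exists. The values are at risk only. A proxy report after death is, however, still retrospective and made with the outcome known.
- **That 21% is the expected loss.** It is close to a worst case. It assumes no proxy or record for any deceased patient, and adds 10% non-response among survivors. The Sample size section applies 90% to the whole subgroup without a separate deduction for deaths. The mortality inputs also describe hip fracture patients in general from injury, whereas this cohort is operated and approached for consent after surgery.
- **That the adjusted models drop many extra patients.** The planned formal analyses use EQ-5D as the response. The dead and the non-responders already lack a 4-month EQ-5D, so a missing covariate removes few more. The article does not specify adjustment of mortality models for these two items, so loss there is a consequence for any embedded study that chooses to adjust.

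Nor does the article show that recall of broad categories, such as own home or nursing home, is in fact distorted. That is a risk, of unknown size.

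**Conclusion.** The point holds in a limited form. The Outcome data section places prefracture residence and mobility at the 4-month contact, names no earlier study collection point for them, and does not use the inpatient history that the article says is documented. This is a stated timing, so it is more than detail left to a fuller protocol.

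Followed literally, the rule gives baseline values obtained after the outcome is known. For an assumed 12-13% of patients it makes them depend on a proxy or general practitioner. Overall loss could lie anywhere from about 9-10% to about 21%, depending mainly on how often such sources respond. These figures rest on the interpolated mortality, on the article's rates applying to enrolled patients, and on 10% non-response.

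The main harm is outcome-related recall in adjusted and change-from-prefracture analyses, with loss of covariates in mortality analyses second. A reader might infer that the cohort's baseline data are invalid or that the EQ-5D regressions are seriously depleted. The article supports neither. The passage should be corrected because the risk is avoidable at almost no cost.

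**What to change.** Reword the residential and mobility paragraphs under Outcome data along these lines: *Prefracture residential and mobility status will be recorded at baseline during the index admission, from the documented history. Current residential and mobility status will be collected at 4 months.* State that the baseline values are the ones used in adjusted and change-from-prefracture analyses.

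If prefracture status is already recorded in hospital, only the text changes. If it is not, two items move from the 4-month form to the baseline form, using information that the pathway already has staff obtain. Sample size and follow-up schedule are unaffected.
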